**Figure 1 f1:**
[figure not shown]
Study timeline.

### Data collection

Demographic characteristics, comorbidities, clinical data, and severity of illness will be collected at baseline for all patients (Table 2S - Supplementary Material). Additional data on the procedure characteristics will also be collected (Table 3S - Supplementary Material). During and after the procedure, hemodynamic data will be registered at the following time points: 1 minute before induction; every 2 minutes during the first 10 minutes after the administration of the study medication; every 5 minutes up to one hour after induction (Table 4S - Supplementary Material). Doses of vasoactive drugs will also be recorded. Any adverse events occurring within the first hour post-induction, including death, cardiac arrest, arrhythmias, bronchoaspiration, and laryngospasm, will be documented.

Patients will be followed until hospital discharge, censored at day 60^th^, to determine the need for mechanical ventilation up to day 7, vital status at day 7, in the ICU, and in the hospital. Patients who are withdrawn from the study for safety reasons (excluding those who withdraw consent) will be included in the analysis on an intention-to-treat basis.

Data will be collected via electronic forms using the RedCap platform and securely stored. The investigators will complete the forms, using specific passwords for access. Training will be provided for all personnel involved in the study to ensure high-quality data collection. The principal investigator will be available to answer any questions regarding form completion. Data consistency will be periodically reviewed, and any discrepancies will be addressed by contacting the sites for clarification and correction.

### Ethical considerations

The Research and Ethics Committee of the UNIFESP approved this study under approval number 48163721.9.1001.5505, followed by approval from the *Hospital SEPACO* Ethics Committee. All patients or their legally authorized representatives will provide signed informed consent. Given the emergency nature of the study and considering that both interventions are routinely used in clinical practice, consent may be obtained retrospectively.

Patient inclusion will begin only after formal ethical approval. Investigators are committed to following all clinical best practices and adhering to the requirements of the National Health Council Resolution 510/16, ensuring the ethical conduct of the study and the safety of participants.

### Statistics

#### Sample size calculation and interim analysis

We plan to randomize an adequate number of patients to ensure 170 patients who are successfully intubated and consented to participate. Based on the assumption that some patients may be randomized but not intubated, or consent could not be obtained, we anticipate that more than 170 patients will need to be randomized. This sample size will provide 90% power with an alpha of 0.05 to detect a 10mmHg difference in the lowest MAP within the first 10 minutes after induction for intubation, assuming a standard deviation of 20mmHg. The study steering committee determined the minimum clinically important difference of 10mmHg.

An interim analysis will be performed after the inclusion of 80 patients to assess the safety profile of the intervention concerning the primary outcome. The study will not be terminated for benefit or futility unless a safety threshold of p < 0.01 is reached, particularly if significant differences in MAP favor the propofol group. This analysis will be conducted by an independent external DSMB, which will remain unblinded to group allocation. The DSMB will also review adverse events and the safety profile to provide recommendations.

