### Randomization and concealment

Patients will be randomized to receive either ketamine or propofol via a central, web-based, automated randomization system (RedCap UNIFESP), accessible 24 hours per day. An external individual not involved in the study will generate a list using the randomization tool on random.org. Patients will be randomized in a 1:1 ratio, in blocks of variable size, stratified according to study site and use of vasopressors. The central automated system will maintain the confidentiality of the randomization sequence. Site investigators will be unaware of the block sizes, ensuring adequate concealment of the randomization sequence. The system will allow only one randomization per patient, and study team members at each site will be responsible for enrolling patients and assigning interventions. The flowchart is available in figure 1S (Supplementary Material).

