For secondary binary and exploratory outcomes, logistic regression will be used, with the effect estimate expressed as odds ratios (ORs) and 95%CIs, with their respective p values. Deaths within the specified ranges will be considered zero free days for outcomes related to free days (ventilator-free days in 7 days). Logistic regression models for ordinal data will report proportional ORs. The frequency of adverse events will be expressed as counts and percentages, and comparisons will be made using the Chi-squared test for categorical variables. Secondary outcomes will not be adjusted for covariates.

For the primary outcome, a pre-specified subgroup analysis will evaluate the following groups: patients < 70 *versus* ≥ 70 years old; patients with a Sequential Organ Failure Assessment (SOFA) score < 8 *versus* ≥ 8 points; patients on vasopressor *versus* without vasopressors; and patients with acute respiratory distress syndrome (ARDS) *versus* those without ARDS. Each subgroup analysis will be performed using linear regression, adjusted for baseline MAP before induction, total vasopressor dose in the first 10 minutes, age, and a random patient intercept. Effect estimates will be reported as mean differences with 95%CIs for each subgroup, with respective interaction p values. We will not adjust for multiplicity.

We will consider a significant two-tailed p level ≤ 0.05. Analysis will be performed using R software in the available version (R Foundation for Statistical Computing), Vienna, Austria.

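### The interim stopping sentence contradicts its safety purpose: read literally, it allows a stop for benefit or futility at p < 0.01 in either direction, with the final test left at 0.05

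*Protocol article*

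**What the plan says.** All but one of the relevant statements are in the protocol article under *Sample size calculation and interim analysis*.

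- Purpose and timing: "An interim analysis will be performed after the inclusion of 80 patients to assess the safety profile of the intervention concerning the primary outcome".
- Rule: "The study will not be terminated for benefit or futility unless a safety threshold of p < 0.01 is reached", followed by "particularly if significant differences in MAP favor the propofol group".
- Planning basis: "This sample size will provide 90% power with an alpha of 0.05 to detect a 10mmHg difference in the lowest MAP", "assuming a standard deviation of 20mmHg".

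The same section says that an independent, unblinded DSMB conducts the analysis and makes recommendations. Under *Statistical analysis*, the final level is given as "We will consider a significant two-tailed p level ≤ 0.05". Neither section assigns any alpha to the interim look, and the sidedness of the 0.01 threshold is not stated.

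**The concern.** The stopping sentence does not fit the purpose given just before it, for three reasons.

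1. Its grammar makes p < 0.01 the condition under which a stop for benefit or futility becomes allowed. A safety-only look would exclude both.
2. The clause on propofol gives one direction emphasis but does not limit the rule to it. A result favouring ketamine at p < 0.01 also meets the threshold.
3. A small p value is evidence of a difference. It cannot be a criterion for futility.

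The main thing at stake is the conduct of the trial. If ketamine is clearly ahead at 80 patients, the sentence supports either decision, and an unblinded board would be choosing its reading after seeing the direction of the result. A stop would leave 80 patients rather than 170 for outcomes such as cardiac arrest and one-hour mortality, with an estimate that tends to be too large. A smaller matter is that an unadjusted final test at 0.05 after a benefit look does not hold the overall 5%.

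**Working it through.** **Inputs.** Final N is 170, from "ensure 170 patients who are successfully intubated and consented to participate". Allocation is 1:1 (*Randomization and concealment*), so 85 per arm. The difference is 10 mmHg, SD 20 mmHg, final two-sided level 0.05, and the interim is at 80 patients with p < 0.01.

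**Assumptions not in the document.** The 0.01 is two-sided, like the final test. The 80 included patients are all analysable, 40 per arm. A normal approximation without covariate adjustment is used.

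**1. The plan's own figure.** n per arm = 2 × (1.960 + 1.2816)² × 20² / 10² = 84.06, rounded up to 85, so 170 in total. The stated size and power are correct for a design with a single look (power 90.3%, or 90.0% with the t distribution).

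**2. Type I error on the literal reading.** The information fraction is 80/170 = 0.471, so the interim and final Z statistics have correlation √0.471 = 0.686. Overall error = 1 − P(|Z₁| < 2.576 and |Z₂| < 1.960) = 0.0549. Of this, 0.0100 arises at the interim and 0.0449 at the final test. A simulation of 4 million draws gave 0.0551.

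| Variant | Total two-sided error | False ketamine superiority |
|---|---|---|
| Either direction, two-sided 0.01 | 0.0549 | 0.0274 |
| Same, final N 200 (information 0.40) | 0.0557 | 0.0278 |
| Either direction, one-sided 0.01 each way | 0.0614 | 0.0307 |
| Harm-only, two-sided 0.01, stop counted as a rejection | 0.0524 | 0.0250 |

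In the first three rows the last column is half the total, by symmetry.

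**3. Compensating final level.** Setting the overall error to 0.05 with the two-sided 0.01 interim gives a final critical value of 2.006, that is p ≤ 0.0449. Power at 10 mmHg is then 89.7%, so 170 can stay. With a one-sided 0.01 in each direction, the same equation gives 2.082, that is p ≤ 0.037.

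**4. Chance that the ambiguity arises.** Interim standard error = 20 × √(2/40) = 4.47 mmHg. The boundary is 2.576 × 4.47 = 11.5 mmHg. At a true difference of 10 mmHg, P(cross in favour of ketamine) = 1 − Φ((11.52 − 10)/4.472) = 1 − Φ(0.340) = 0.367.

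**5. Estimate given such a stop.** 10 + 4.472 × φ(0.340)/0.367 = 10 + 4.472 × 0.3766/0.3670 = 14.6 mmHg, about 46% above the true value. Averaged over all trials under the literal rule, stopped or not, the estimate is about 10.9 mmHg.

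**The case against.** The strongest reply is that the context points to a harm rule. The look is described as a safety assessment, the threshold is called a safety threshold, and the only direction named is the one in which ketamine does worse. On that reading the chance of a false claim of ketamine superiority stays at 0.025, and the final 0.05 needs no change. This is a plausible account of the intent, and it is why the alpha point can only be conditional. It does not rescue the sentence, which still says something else.

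The size is also small on the literal reading: 5.5% against 5%, removable at the cost of a fraction of a percentage point of power. That stands. So does the reply on exaggeration. Overestimation after an early benefit stop occurs in any design with a benefit boundary, and the average bias over all trials is only about 0.9 mmHg.

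A further reply is that sidedness and operating detail usually sit in a DSMB charter or analysis plan, which is not shown, and that the board only recommends. Missing sidedness alone would therefore not be a finding. But the article does state a rule, and the rule contradicts its declared purpose. A clear charter would not correct the published text.

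A reader might infer that the trial fails to control its type I error, or that the board is set to stop for ketamine benefit. The documents support neither. Both follow only from the literal wording, and the surrounding text leans the other way.

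**Conclusion.** The stopping sentence is faulty as written and should be corrected. It contradicts the safety purpose of the look, does not restrict direction, and uses a small p value as if it could signal futility. The practical consequence is an ambiguous instruction in a situation with about a 37% chance of arising if the design effect is true. That figure rests on SD 20 mmHg, 40 analysable patients per arm and a two-sided 0.01; covariate adjustment or losses before analysis would move it.

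The alpha consequence is conditional and modest: about 5.5% overall on the literal reading, 5.6% at an information fraction of 0.40, and 6.1% if the 0.01 is one-sided in each direction. These error rates do not depend on the SD. On a harm-only reading, the false-positive rate for ketamine superiority is not inflated at all. The planned N and power are not in dispute.

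**What to change.** Reword the sentence so that it states direction, sidedness and whether a benefit stop is allowed. Preferred text, for the protocol and the DSMB charter:

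> The DSMB may recommend stopping only if lowest MAP is lower with ketamine at two-sided p < 0.01. The trial will not stop for benefit or futility. A stop under this rule will be reported as a safety stop, not as a significant efficacy result.

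The final 0.05 can then stand. The last sentence is needed because counting a harm stop as a rejection would bring the total error to about 5.2%.

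If stopping in both directions is really wanted, say so, set the final level to about p ≤ 0.045 for a two-sided 0.01 interim (about 0.037 if one-sided in each direction), and remove futility from the small-p criterion. With the two-sided interim, power is about 89.7% and N stays at 170.

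The cost is one or two sentences. The first option gives up an early benefit stop that the text appears not to want; the second accepts a slightly stricter final test.

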#### Statistical analysis

Our primary analysis will follow a modified intention-to-treat (mITT) approach. As clinical management might change after randomization, we expect that some patients who will be randomized will not be intubated. Similarly, as we will use a deferred (opt-out) consent process, some patients (or representatives) might not consent. Thus, our mITT analysis will include only those patients who will be intubated and who consent to participate. The data analysis will be performed after submitting the protocol paper and analysis plan for publication.

Categorical variables will be expressed as counts and percentages. Continuous variables will be presented as means and standard deviations (SD) or medians with interquartile ranges (IQR, 25th -75th percentile) as appropriate. For all outcomes, including the primary outcome, we will not impute missing data, and the number of missing values will be clearly presented in tables. Treatment adherence will be reported as each group's mean (SD) number of successful medication administrations.

The primary outcome (lowest MAP within the first 10 minutes post-induction) will be analyzed using a linear regression model, adjusted for baseline MAP before induction, total vasopressor dose in the first 10 minutes, age, and a random patient intercept. A MAP value of 10mmHg (the average cardiovascular filling pressure) will be considered in patients with cardiac arrest.^(14)^ Other vasopressors will be converted to noradrenaline dose equivalents. A per-protocol analysis will be performed, including only patients who received the assigned medication. Additionally, we conducted sensitivity analysis considering the lowest measured blood pressure before cardiac arrest and an unadjusted analysis. In all primary outcome analyses, the effect estimate will be expressed by the mean difference with 95% confidence intervals (95%CI) and p values reported.

For secondary binary and exploratory outcomes, logistic regression will be used, with the effect estimate expressed as odds ratios (ORs) and 95%CIs, with their respective p values. Deaths within the specified ranges will be considered zero free days for outcomes related to free days (ventilator-free days in 7 days). Logistic regression models for ordinal data will report proportional ORs. The frequency of adverse events will be expressed as counts and percentages, and comparisons will be made using the Chi-squared test for categorical variables. Secondary outcomes will not be adjusted for covariates.

For the primary outcome, a pre-specified subgroup analysis will evaluate the following groups: patients < 70 *versus* ≥ 70 years old; patients with a Sequential Organ Failure Assessment (SOFA) score < 8 *versus* ≥ 8 points; patients on vasopressor *versus* without vasopressors; and patients with acute respiratory distress syndrome (ARDS) *versus* those without ARDS. Each subgroup analysis will be performed using linear regression, adjusted for baseline MAP before induction, total vasopressor dose in the first 10 minutes, age, and a random patient intercept. Effect estimates will be reported as mean differences with 95%CIs for each subgroup, with respective interaction p values. We will not adjust for multiplicity.

We will consider a significant two-tailed p level ≤ 0.05. Analysis will be performed using R software in the available version (R Foundation for Statistical Computing), Vienna, Austria.

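### The primary analysis set depends on intubation and on consent that may come after the outcome, so patients who die early may be lost if no signature is obtained

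*Protocol article*

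**What the plan says.** All references are to the protocol article.

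- **Statistical analysis** defines the primary set: "our mITT analysis will include only those patients who will be intubated and who consent to participate". Two reasons are given. The first is "As clinical management might change after randomization, we expect that some patients who will be randomized will not be intubated". The second is "as we will use a deferred (opt-out) consent process, some patients (or representatives) might not consent".
- **Sample size calculation and interim analysis** sets the target as "170 patients who are successfully intubated and consented to participate" and expects to randomize more because "some patients may be randomized but not intubated, or consent could not be obtained".
- **Ethical considerations** states: "All patients or their legally authorized representatives will provide signed informed consent". It adds that consent may be retrospective. **Trial organization and oversight** likewise says written consent will be obtained from all patients or their representatives.
- **Outcomes** places the primary outcome, the lowest MAP, in the first 10 minutes after induction. Death and cardiac arrest within one hour are secondary outcomes.
- **Statistical analysis** also assigns 10 mmHg to patients with cardiac arrest, imputes no missing data, and names three further primary-outcome analyses: per-protocol, lowest pressure before arrest, and unadjusted.
- **Data collection** keeps patients withdrawn for safety reasons in the analysis, except those who withdraw consent.

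**The concern.** Anyone given the induction agent has entered the outcome window. Membership of the primary set, however, is decided by what follows: whether the patient ends up intubated, and whether consent is given, possibly after the outcome is known. If early death or arrest makes either condition harder to meet, exclusion depends on an outcome that the drug may influence.

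The consent wording matters most. Under opt-out, a patient who dies before anyone is approached stays in. Under signed consent from all, with losses where consent is not obtained, the same patient is out unless a representative signs. These are the patients who would carry the 10 mmHg value, so the two readings give different data sets at the lower extreme of the outcome. One-hour death and arrest are exposed in the same way if they are analysed on the same set. Treating staff know the allocation, so similar handling in the two arms cannot be taken for granted.

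**Working it through.** **1. The plan's own figure.** Inputs from the sample size section: difference 10 mmHg, SD 20 mmHg, alpha 0.05 (two-sided, from the analysis section), power 90%, 1:1 allocation.

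n per arm = 2 × (1.960 + 1.282)² × 20² / 10² = 84.1, rounded up to 85, so 170 in total. Power at 85 per arm is 0.903 by the normal approximation and 0.900 by the noncentral t. The figure reproduces; the problem is who enters the set.

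**2. When each condition is settled.**

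| Condition | Can it be settled after induction? | Who could be lost |
|---|---|---|
| Intubated (analysis section) | Yes: laryngoscopy comes one minute after the neuromuscular blocker | Arrest or death before the tube is placed |
| Successfully intubated (target count only) | Yes: failed attempts are foreseen under Interventions | A failed airway, if this wording defines the set |
| Consent, opt-out | Yes, deferred | Those who refuse |
| Consent, signed by all | Yes, may be retrospective | Those who refuse, and those with no signature obtained |

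**3. Do other rules close the gap?** The 10 mmHg rule and the pre-arrest sensitivity analysis act only on patients already in the set. The rule for safety withdrawals does not cover failed intubation or consent never obtained. None of the named analyses covers all randomized or all induced patients.

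**4. Size per patient.** Assumption: mean lowest MAP without arrest of 60 or 65 mmHg. One arrest scored at 10 mmHg and dropped from an 85-patient arm moves that arm's mean by

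- (60 − 10)/85 = 0.59 mmHg, or
- (65 − 10)/85 = 0.65 mmHg.

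**5. Size for the contrast.** Let μ be an arm's mean without arrest, p its arrest rate and e the share of arrests excluded.

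- All kept: (1 − p)μ + 10p
- Share e lost: [(1 − p)μ + 10p(1 − e)] / [(1 − p) + p(1 − e)]

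Worked case, μ = 65 in both arms, rates 8% v 3%, all arrests lost. Kept: 0.92 × 65 + 0.8 = 60.60 and 0.97 × 65 + 0.3 = 63.35, a difference of 2.75. Lost: 65 and 65, a difference of 0. The shift is 2.75 mmHg.

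The ranges below cover μ = 60 or 65 in the arm with more arrests, with the other arm's μ equal or 10 mmHg higher. Rates and shares lost are assumptions, because the article gives none.

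| Arrest rates | Shift, half lost (mmHg) | Shift, all lost (mmHg) |
|---|---|---|
| 2% v 2% | 0 to 0.1 | 0 to 0.2 |
| 3% v 1% | 0.4 to 0.5 | 0.9 to 1.1 |
| 5% v 2% | 0.6 to 0.8 | 1.3 to 1.7 |
| 8% v 3% | 1.0 to 1.3 | 2.2 to 2.8 |

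In the unequal rows the shift favours the arm with more arrests. In an arm of 85, 8% is 6.8 patients and 3% is 2.6, so the bottom row means losing about seven patients from one arm and three from the other. These are shifts in raw means; covariate adjustment does not bring excluded patients back.

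**The case against.** The strongest reply has four parts.

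- **Intubation.** The stated reason concerns procedures that are called off, in patients with no induction and no outcome. Once induced, a patient receives rocuronium at once, and failed attempts pass to another operator or to adjunct devices, so few induced patients would end up not intubated. The word *successfully* stands only in the recruitment target. This largely holds. A reader might infer that failed airways and peri-intubation arrests are routinely removed; the text does not support that. It leaves a narrow opening, because the rule is not limited to events before induction and the two sections differ.
- **Intent.** Scoring arrest at 10 mmHg and keeping safety withdrawals show a wish to count the worst outcomes. That is fair, but neither rule overrides the consent condition.
- **Consent.** A representative may sign, so death does not in itself prevent consent, and consent *may* be retrospective, so it need not always follow the outcome. What may be kept without consent depends on an ethics approval that is not shown. A reader might infer that the plan excludes early deaths; no section says so. What stands is that the sections conflict on exactly this case. That is a contradiction in the printed text, beyond a detail left to a fuller document.
- **Size.** Four arrests lost from one arm and none from the other would give 4 × 0.59 = 2.4 mmHg, but nothing in the article makes that pattern likely. With equal rates the shift is close to zero.

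**Conclusion.** The point holds in a limited form. The primary set and the target count rest on conditions that can be settled after the study drug and after the outcome. The consent sections disagree on whether a patient who dies early without a signature is analysed. Consent is the main route for losing the worst outcomes; the intubation condition is a minor one.

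The shift in the mean difference runs from about 0 to about 2-3 mmHg against the 10 mmHg target. It rests on assumed arrest rates, an assumed mean of 60 to 65 mmHg and an assumed share lost. The upper end needs unequal rates and the loss of every arrest. It would be wrong to conclude that the result must favour one named drug: the shift favours whichever arm loses more arrests, and the documents do not say which that would be. If one-hour deaths and arrests are few, one or two exclusions would weigh heavily, but the article gives no expected counts from which to size this.

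**What to change.** 1. Define the primary set as all randomized patients in whom the intubation procedure was started (any induction drug given or laryngoscopy attempted), analysed as randomized whatever the intubation result. Including laryngoscopy keeps a patient intubated without any hypnotic, whom a set based on the hypnotic alone would drop. Patients whose procedure is called off beforehand remain outside, as the authors intend.
2. Remove *successfully* from the sample size section, so that the 170 are counted on the same set as the one analysed.
3. Reconcile the four sections on consent (oversight, ethics, sample size, analysis). As far as the ethics approval allows, exclude only on explicit refusal or withdrawal, and not because consent could not be obtained. State what happens when a patient dies before consent is sought.

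The cost is a wording change, a check with the ethics committee about data from patients who die before contact, and possibly a few more patients analysed than under the present rule. The 170 and the 90% power do not change. The start of the procedure still comes after open-label allocation, so some post-randomization selection remains, but it no longer depends on the outcome.

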### Blinding

Blinding of healthcare professionals is not feasible due to the distinct visual differences between propofol (a white lipid emulsion) and ketamine (colorless). However, data collectors, outcome assessors, and statisticians will remain blinded to group allocation to minimize bias.

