If the first attempt is unsuccessful, the patient will be reoxygenated before another attempt is made. If intubation remains unsuccessful after two attempts, a qualified alternate operator or adjunct devices will be utilized. If additional medications are required, the study hypnotic agent will be used, with dosing at the discretion of the attending team. All intubation steps will follow a strict protocol, and patients will undergo an intubation checklist as per routine in the participating units (Figure 2S - Supplementary Material). Continuous monitoring will be performed using electrocardiography, pulse oximetry, and invasive or non-invasive blood pressure monitoring. The monitor will proceed with measurements every 2 minutes for patients with noninvasive blood pressure measurement. The use of vasoactive drugs before induction will be initiated only if the patient's mean arterial pressure (MAP) is below 65mmHg, following the institutional protocol. Doses of vasoactive drugs can be adjusted during the procedure at the discretion of the ICU team. In both groups, general management, such as pre-oxygenation, ventilatory support, and use of adjunctive devices, will follow the ICU protocol (Supplementary Material). Data on adherence to the study protocol, including successful medication administration, will be collected for all patients who undergo intubation in both groups. Any instances patients do not receive the assigned medication will be documented, including the reason for non-administration.

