### Outcomes

The study's primary outcome is the lowest MAP recorded within the first 10 minutes following the induction for intubation.

Secondary outcomes include:

–Average MAP within the first hour after induction.–Mortality within the first hour after induction.–Cardiac arrest within the first hour after induction.–Occurrence of severe hypotension, defined as systolic blood pressure (SBP) < 80mmHg, within 1 hour after induction.–Occurrence of severe hypoxemia, defined as peripheral oxygen saturation (SpO_2_) < 85%, within one hour after induction.–Time for successful intubation.

Tertiary outcomes include:

–The number of intubation attempts.–The highest HR within 1 hour after induction.–The total dose of vasopressors administered within the first 24 hours, using the noradrenaline equivalent dose.–Mean change in vasopressor dose (norepinephrine equivalent) from baseline to hour 1.–Ventilator-free days within the first 7 days, defined as the number of days on which individuals are able to breathe spontaneously without any invasive ventilatory assistance, ascribing zero days to those who die within 7 days.–Mortality at day 7.–ICU mortality.–Hospital mortality.

Safety outcomes will be assessed during the first 10 minutes following induction, and will include:

–Hypertension, defined as SBP > 180mmHg.–Laryngospasm, as reported by the physician in charge of intubation.–Bradycardia, defined as HR < 45 bpm.–Arrhythmias.–Bronchoaspiration, defined as the presence of gastric content aspirated into the airway during intubation.

All outcome data will be presented as specified on the electronic supplemental materials (Table 1S - Supplementary Material). The trial sequence is available in figure 1.

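### The primary and subgroup models adjust for vasopressor dose given after the study drug, so the coefficient need not estimate the total ketamine-propofol difference in lowest MAP

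*Protocol article*

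**What the plan says.** Under Outcomes: "The study's primary outcome is the lowest MAP recorded within the first 10 minutes following the induction for intubation". Under Statistical analysis, this outcome will be "analyzed using a linear regression model, adjusted for baseline MAP before induction, total vasopressor dose in the first 10 minutes", together with age and a random patient intercept. The subgroup models carry the same term: "Each subgroup analysis will be performed using linear regression, adjusted for baseline MAP before induction, total vasopressor dose in the first 10 minutes".

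Three other statements bear on that term:

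- Interventions: "Doses of vasoactive drugs can be adjusted during the procedure at the discretion of the ICU team".
- Blinding: "Blinding of healthcare professionals is not feasible due to the distinct visual differences". Those who adjust the dose therefore know the drug.
- Outcomes, tertiary list: "Mean change in vasopressor dose (norepinephrine equivalent) from baseline to hour 1", together with the 24-hour vasopressor total. The protocol itself treats later vasopressor dose as something the treatment may change.

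An unadjusted analysis of the primary outcome is planned as a sensitivity analysis. Randomization is stratified by site and vasopressor use.

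**The concern.** The covariate is not a baseline characteristic. The sentence that defines the model marks MAP as a pre-induction value and gives the dose the same ten-minute window as the outcome, so the natural reading is that the dose is summed after the study drug. It is then both a possible consequence of the drug and a response to the pressure being measured.

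Holding it fixed compares the arms as if they had needed equal pressor support. If one agent lowers pressure more and staff respond with more vasopressor, part of the drug effect is credited to the dose term. Adjustment also links the arms through any unmeasured cause of both low pressure and high dose, which randomization had balanced.

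The objective is whether ketamine reduces hypotension compared with propofol. That is a total effect, and no direct-effect or mediation aim is stated. At stake are the headline estimate, its power, and every subgroup estimate and interaction test.

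**Working it through.** **1. What the sample size refers to.** Inputs from the sample size section: difference 10 mmHg, SD 20 mmHg, two-sided alpha 0.05, power 90%, 1:1 allocation.

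n per arm = 2 × (1.960 + 1.282)² × 20² / 10² = 84.1, so 85 per arm and 170 in total. With 85 per arm the standard error is 20 × √(2/85) = 3.07 and power is 90.3% (normal) or 90.0% (t-test). The stated figure reproduces, as a plain two-group difference with nothing held fixed after randomization.

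**2. How adjustment acts when dose follows pressure.** The documents give no dose-response figure, so what follows is assumption. Let the nadir L differ by τ between arms, with variance σ² given arm and baseline. Let dose be V = b(70 − L) + noise of variance ω². Regressing L on arm, baseline and V gives an arm coefficient of

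τ × ω² / (b²σ² + ω²).

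The effect shrinks by the share of dose variance that the nadir explains. With τ = 10, σ = 18.5 and ω = 5:

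- b = 0.1: 10 × 25 / (3.4 + 25) = 8.8
- b = 0.3: 10 × 25 / (30.8 + 25) = 4.5
- b = 0.5: 10 × 25 / (85.6 + 25) = 2.3

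Doses cannot be negative, which weakens the shrinkage. Simulation with that floor (1,000,000 patients per setting; baseline MAP slope 0.5, outcome SD about 20; g is the assumed rise in MAP per unit of dose) gave:

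| b | g | Total effect (baseline MAP and age only) | Planned model |
|---|---|---|---|
| 0.1 | 0 | 10.0 | 9.1 |
| 0.3 | 0 | 10.0 | 5.8 |
| 0.5 | 0 | 10.0 | 4.1 |
| 0.1 | 0.5 | 9.8 | 9.1 |
| 0.3 | 0.5 | 9.1 | 5.8 |
| 0.5 | 0.5 | 8.5 | 4.0 |

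In 1,500 simulated trials of 170 patients at b = 0.3, g = 0, power was about 75% with the dose term and 94% with baseline MAP and age only.

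**3. A second assumed model.** Nadir = 60 + 0.5 × (baseline − 80) − 5 × severity + effect + N(0, 15). Dose = baseline dose + k × max(0, 65 − nadir) + noise. For k = 0.002, 0.005 and 0.01, a true 10 mmHg is estimated at about 9.5, 8.3 and 6.5. Replacing the 10-minute dose by the pre-induction dose, or not adjusting, returns about 10.

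Adding 0.05 to every propofol-arm dose, unrelated to pressure, gives about 7.0, 5.0 and 2.9. With a true effect of zero it gives −2.7 to −3.6. That addition is not small: the mean pressure-driven dose in the propofol arm is about 0.02, 0.05 and 0.10, so 0.05 is 2.5, 1 and 0.5 times the whole average response.

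**4. Where the bias vanishes or reverses.**

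- Neither pressure nor dose differs by arm: the estimate is about 0, and type I error about 5%.
- Ketamine lowers dose directly by 2 units, each unit raises MAP by 1, the direct effect is 10, and dose shares no unmeasured cause with MAP: the total effect is 10 − 2 × 1 = 8.0 and the planned model returns 10.0, which is larger.
- The same, with unmeasured severity driving both dose and MAP: total 8.0, planned model 7.0.

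**The case against.** The strongest reply is that the protocol already plans an unadjusted analysis with mean difference, confidence interval and p value. In a randomized comparison that analysis is unbiased for the total effect as far as this covariate is concerned, and it matches the sample size calculation. Losing baseline MAP costs precision, not validity. This stands, and it lowers the risk that the problem goes unseen. It does not cure it: the prespecified headline remains the dose-adjusted one, and no unadjusted counterpart is stated for the subgroup models.

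A second reply is that every magnitude rests on assumed dosing behaviour. That also stands, including for the random spread assumed in the doses. The weakest setting in step 3 loses only 0.5 mmHg.

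Some stronger readings are tempting but go beyond the text:

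- A reader might infer that a true benefit is always shrunk. Step 4 shows that the direction depends on the mechanism.
- A reader might infer a spurious advantage for propofol from allocation-driven dosing. The protocol permits discretion but documents no such behaviour, and the figures for it need a large assumed extra dose.
- A reader might infer that drugs given during an arrest enter the covariate, because "Other vasopressors will be converted to noradrenaline dose equivalents". The article does not say whether arrest boluses count.
- A reader might extend the point to the interim look. No model is named for it.

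**Conclusion.** The model is wrong as written for the trial's question. It conditions on a variable measured after the study drug, in the outcome window, and open to titration by unblinded staff. Whenever pressure or dosing differs by arm, which is the trial's own hypothesis for pressure, the primary and subgroup coefficients need not estimate the total ketamine-propofol difference in lowest MAP.

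If dose mainly follows low pressure, the pull is toward zero: a true 10 mmHg at roughly 6.5 to 9.5 under one assumed model and 4.1 to 9.1 under another, and lower still if extra vasopressor goes to the propofol arm because of the allocation. These are illustrations. Only the 10 mmHg difference, the SD of 20 and the 170 patients come from the protocol. A claim of certain bias, or of bias in a known direction, is not supported.

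**What to change.** In the primary model and all subgroup models, delete the 10-minute vasopressor term. Put in its place either vasopressor dose before induction, in noradrenaline equivalents, or the stratification factor vasopressor use. Keep baseline MAP and age, and add site, the other stratification factor.

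The stratum is fixed at randomization. The earliest hemodynamic time point listed under Data collection is 1 minute before induction, which precedes the study drug but may follow knowledge of the allocation; the stratum is therefore the cleaner choice if the two diverge.

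Report the 10-minute vasopressor dose by arm as an outcome, and label any dose-adjusted model exploratory.

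The cost is one covariate, changed before analysis. Vasoactive doses are already recorded, and the tertiary outcome on dose change to hour 1 needs a baseline dose anyway. The sample size does not change.
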